#### Implementation

##### Feasibility

The treatment will be considered feasible if the 200 study participants are recruited by screening at least 300 HIV+ GBV+ women, if each completer attends ≥80 % of IPT sessions, attrition is fewer than 50 study participants and if one or fewer therapists voluntarily drop out of the training course and trial.

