### Participant recruitment, consent, inclusion and exclusion criteria and randomization

#### Recruitment

HIV+ women will be recruited by informing FACES HIV care providers of the study (provider referral) and giving informational talks to FACES patients who are waiting for HIV appointments (self-referral). Consecutive HIV+ women will be consented and screened for inclusion in this study until the desired sample size is reached. Women who do not meet study criteria will be referred to existing FACES psychosocial care and GBV resources as indicated below.

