##### Feasibility

The treatment will be considered feasible if the 220 study participants are recruited by screening at least 300 HIV+ GBV+ women, if each completer attends ≥80 % of IPT sessions, attrition is 50 or fewer study participants and if 50 % or fewer of the study therapists voluntarily drop out of the training course and trial.

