##### Feasibility and fidelity

Feasibility and Fidelity measures will be assessed by sample means and proportions, with 95 % confidence intervals, and compared to pre-specified benchmarks (see above).

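### The feasibility benchmark sets a minimum, not a maximum, on the number of women screened, so once the target is recruited a low screening yield passes and a high one fails

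*Protocol article*

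**What the plan says.** The feasibility rule appears twice in the protocol article.

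- Under Statistical analysis, Implementation, Feasibility: "The treatment will be considered feasible if the 200 study participants are recruited by screening at least 300 HIV+ GBV+ women".
- Under Implementation outcomes, Feasibility: "The treatment will be considered feasible if the 220 study participants are recruited by screening at least 300 HIV+ GBV+ women".

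The targets differ (200 and 220), but the direction of the screening bound is the same. In both places the recruitment condition is joined to three others: session attendance of at least 80%, a limit on attrition and a limit on therapist drop-out. In the statistical analysis section those two limits read "attrition is fewer than 50 study participants" and "one or fewer therapists voluntarily drop out of the training course and trial".

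The Recruitment section says when screening ends: "Consecutive HIV+ women will be consented and screened for inclusion in this study until the desired sample size is reached". The article states no maximum number screened and no recruitment deadline.

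The section on feasibility and fidelity analysis commits to using the rule: "Feasibility and Fidelity measures will be assessed by sample means and proportions, with 95 % confidence intervals, and compared to pre-specified benchmarks (see above". The abstract lists feasibility among the primary implementation outcomes.

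**The concern.** A benchmark for recruitment feasibility should fail when filling the trial takes too much screening. A minimum number screened works the other way: more screening per woman enrolled can never cause a failure, and less can.

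The other three conditions behave as expected. Attendance is a floor on a desirable quantity, and attrition and therapist drop-out are ceilings on undesirable ones, so each fails on a worse result. Only the screening bound fails on a better one.

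At stake is the feasibility conclusion. The four conditions must hold together, so a trial that recruited very efficiently would formally be declared not feasible whatever the other three showed. In the opposite case, a feasible verdict would be reported as including a recruitment check, although the screening bound had tested nothing about yield.

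**Working it through.** **Inputs.** Target T = 200 (Statistical analysis, Feasibility) or 220 (Implementation outcomes, Feasibility). Screening bound 300 (both). Screening continues until T is reached (Recruitment). The article gives no derivation of the 300, so there is no planning figure to reproduce beyond the yield it implies.

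**Step 1: yield at the bound.** Yield = T / number screened.

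- T = 200: 200/300 = 66.7%.
- T = 220: 220/300 = 73.3%.

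**Step 2: apply the rule, T = 200 reached.**

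| Screened | Yield | As written (≥ 300) | Ceiling (≤ 300) |
|---|---|---|---|
| 250 | 80.0% | fails | passes |
| 299 | 66.9% | fails | passes |
| 300 | 66.7% | passes | passes |
| 400 | 50.0% | passes | fails |
| 1,000 | 20.0% | passes | fails |
| 2,000 | 10.0% | passes | fails |
| 5,000 | 4.0% | passes | fails |

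With T = 220 the pattern is the same: 220/299 = 73.6% fails and 220/400 = 55% passes.

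**Step 3: probability of passing by true yield.** Assume that each screened woman enrols independently with probability y and that screening runs until T is reached. The rule as written is met if fewer than T enrol among the first 299 women. A ceiling is met if at least T enrol among the first 300.

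- P(pass as written) = 1 − P(X ≥ T), X ~ Binomial(299, y)
- P(pass with ceiling) = P(X ≥ T), X ~ Binomial(300, y)

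| True yield y | As written, T = 200 | Ceiling, T = 200 | As written, T = 220 | Ceiling, T = 220 |
|---|---|---|---|---|
| 10% to 50% | 1.00 | 0.00 | 1.00 | 0.00 |
| 60% | 0.99 | 0.01 | 1.00 | 0.00 |
| 66.7% | 0.50 | 0.53 | 0.99 | 0.01 |
| 70% | 0.11 | 0.91 | 0.90 | 0.11 |
| 75% | 0.0007 | 0.9995 | 0.26 | 0.77 |
| 80% | 0.00 | 1.00 | 0.003 | 0.998 |

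As written, the chance of passing falls as yield improves. With a ceiling it rises.

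**Step 4: other ways to fail.** The condition also requires that T women be recruited. If recruitment stopped short of T, it would fail whatever the number screened. Steps 2 and 3 are therefore conditional on reaching T.

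**The case against.** **A minimum screening reach may have been intended.** The identical wording in two places makes a slip less certain. The authors may have meant that the clinic can bring at least 300 women of the target population to screening and enrol the target from among them. That reading is possible, but it does not rescue the rule: enrolling 200 from 250 still fails and 200 from 2,000 still passes. If reach was intended, it needs its own statement, separate from the recruitment verdict.

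**Poor recruitment can still fail.** A reader might infer that the component always passes or says nothing about recruitment. The article does not support that. Missing the target fails the condition, and the Recruitment section's stopping rule is a plan, with no guarantee that one clinic holds enough eligible, consenting women. This objection stands, and it limits the point to screening yield once the target is reached.

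**The population label.** A reader might also infer that screening spent on women without gender-based violence is excluded from the count, because the rule names HIV+ GBV+ women while the Recruitment section screens HIV+ women. The article uses that label throughout for its study population, so treating it as a counting rule is an inference. What stands is that the denominator is not stated clearly.

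**Simply capping all screening at 300 would be a new benchmark.** This also stands. As an illustration from the Background section, if 57% of women screened were GBV-affected (the regional figure for physical violence), 300 screened would give at most 0.57 × 300 = 171, below either target. At 71%, the top of the quoted range for sub-Saharan Africa, the maximum is 213. That is below 220, and reaching 200 would need 200/213 = 94% of them to qualify and enrol. Referral may enrich the pool, so these figures only show that 300 cannot be carried over to a wider denominator without thought.

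**Importance.** The article gives effectiveness as its primary goal. No treatment-effect estimate, error rate or sample size depends on this clause, and it cannot by itself produce a feasible verdict.

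**Conclusion.** The concern holds in this form: the screening bound runs the wrong way in both places where it is stated. Given that the target is recruited, every yield of 66.7% or less passes (73.3% or less with the target of 220) and only a higher yield fails. The component cannot detect poor screening yield, and it penalises efficient recruitment.

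The cut points are plain arithmetic on the article's own numbers. They rest on one condition, that the target is reached, which is the planned course because no cap or deadline is stated. The probabilities in the working also assume independent enrolment at a constant yield; the direction of the result does not depend on that.

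This is a stated threshold against which the article commits to comparing results, so it is not a detail left to a fuller document. Severity is moderate: it affects a primary implementation outcome through one of four joint components and leaves the effectiveness analysis untouched.

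**What to change.** 1. In both Feasibility paragraphs, turn the bound into a ceiling (no more than 300 screened, for the population for which the 300 was set), or state the equivalent minimum yield.
2. Use one target. The choice moves the cut: 66.7% for 200, 73.3% for 220.
3. State which women form the denominator. If every woman who starts eligibility screening is counted, set a ceiling for that denominator and give its basis; do not carry over the 300.
4. Trial status says that recruitment is active. Date the change and state whether screening yield was already known when it was made.
5. Report enrolled/screened with the 95% confidence interval that the article already plans for feasibility measures.

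The cost is small. Eligibility screening is already captured electronically under Data management, so no new data are needed. The work lies in reconciling the target and agreeing the denominator. The downside is that the criterion can then fail on low yield, and a ceiling fixed during recruitment may not be fully blind to the yield so far, which is why the dating matters.

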##### Acceptability

Interview material will be recorded in audio files, transcribed and translated. Dedoose software will be used to analyze the resulting text using grounded theory. Grounded theory sorts data in three ways: through concepts, categories and propositions. Concepts are identified by seeking conceptual similarities among focus groups/interviews. These concepts are grouped to develop categories of concepts. Categories are then compared and grouped to develop propositions or theoretical constructs about the phenomena of interest. Dedoose software facilitates coding of observations to work toward the theoretical construct. Data will be collected using a “triangulation” technique that compares information from various sources (focus groups, individual interviews) in order to increase the reliability and validity of the findings.

##### Feasibility and fidelity

Feasibility and Fidelity measures will be assessed by sample means and proportions, with 95 % confidence intervals, and compared to pre-specified benchmarks (see above).

##### Cost-benefit analyses

We will use data obtained using the SEARCH economic assessment on the income status of those treated to calculate the economic benefits associated with IPT + TAU versus TAU. The value of these economic benefits will be summarized on a per-person basis and then combined with the cost data to generate a rate or return on IPT + TAU treatment of HIV+ GBV+ women at the FACES clinic.

## Discussion

While the treatment gap for mental health care has been recognized for nearly 20 years, with a few exceptions [51] the majority of studies addressing this gap have used efficacy designs without the benefit of implementation science. This trial will leverage newly defined effectiveness-implementation hybrid designs [5] to gather data on treatment implementation within an HIV care clinic, while testing the effectiveness of an evidence-based treatment for use with a large underserved population (HIV+ GBV+ women) in Kenya. This trial is likely to yield findings that will be generalizable beyond the study population and, if effective, could be scaled up for treatment of HIV+ women in Kenyan HIV clinics and perhaps other countries in sub-Saharan Africa facing a similar HIV-GBV syndemic among women.

Despite awareness of the relationships between GBV, mental disorders and HIV outcomes, this is the first study of which we are aware that intervenes on mental disorders among HIV+ GBV+ women and also collects data on HIV and neurocognitive outcomes. We expect these secondary outcomes to inform women’s HIV care in the region and to shed light on the mechanisms of ART deficits and re-victimization commonly observed among HIV+ GBV+ women.

We recognize a number of limitations in this study. First, generalizability may be limited given that this is a single center study; future multi-center studies will be needed. Another limitation of this study is the TAU control. While TAU includes access to mental health care services, data bearing on the particular efficacy of IPT would be stronger if an active control with similar meeting schedule was included (e.g., weekly, individual supportive therapy). However, given that this study is not intended to test the efficacy of IPT, which has already been established across diverse populations and disorders, but rather to evaluate its effectiveness with a more general and diverse population (HIV+ GBV+ women with MDD and/or PTSD) when implemented by non-specialists within an HIV clinic, we have elected to focus resources on data that will inform scale-up of care.

### Trial status

The trial is actively recruiting participants.

## Abbreviations

ART: antiretroviral therapy
AUDIT: Alcohol Use Disorders Identification Test
AVLT: Auditory Verbal Learning Test
BDI: Beck Depression Scale
BVMT: Brief Visual Memory Test
CAG: Community Advisory Group
CDC: Center for Disease Control
CTS2: Conflict Tactics Scale
DAST: Drug Abuse Screening Test
FACES: Family AIDS Care Education and Services
GBV: gender-based violence
HICs: high income countries
HIV: human immunodeficiency virus
IPT: Interpersonal Psychotherapy
KEMRI: Kenya Medical Research Institute
LMICs: low and middle income countries
MDD: major Depressive Disorder
MINI: Mini International Neuropsychiatric Interview
ODK: CommCare Open Data Kit
PCL-C: Posttraumatic Stress Disorder Checklist-Civilian
PTSD: posttraumatic stress disorder
SAS: Social Adjustment Scale
SEARCH: Sustainable East Africa Research on Community Health
TAU: treatment as usual
THS: Trauma History Screen
UCLA: University of California, Los Angeles
UCSF: University of California, San Francisco
VAS: Visual Analog Scale
WHO: World Health Organization
WHODAS: World Health Organization Disability Assessment Schedule
WHOQOL-BREF: World Health Organization Quality of Life Brief
